#### Fatigue

*The Multidimensional Fatigue Inventory *[50], that will be used to measure fatigue severity, comprises five subscales: general fatigue, physical fatigue, mental fatigue, reduced activity, and reduced motivation [2]. Each subscale includes four items with five-point Likert scales. General fatigue includes general statements about fatigue and decreased functioning and is designed to encompass both physical and psychological aspects of fatigue. Physical fatigue concerns physical sensations related to fatigue. Mental fatigue pertains to cognitive functioning, including difficulty concentrating. Reduced activity refers to the influence of physical and psychological factors on the level of activity. Reduced motivation relates to lack of motivation for starting any activity. Scores on each subscale range from 4 to 20, with higher scores indicating greater fatigue.

#### Sleep quality

*The Pittsburgh Sleep Quality Index *[51] will be used to assess sleep quality and disturbances over a l-month time interval. Nineteen individual items generate seven "component" scores: subjective sleep quality, sleep latency, sleep duration, habitual sleep efficiency, sleep disturbances, use of sleeping medication, and daytime dysfunction. The sum of scores for these seven components yields one global score. This test has been used in previous studies in fibromyalgia patients [52,53].

#### Health-related quality of life

We will determine patients' quality of life with the *Short-Form Health Survey 36 *(SF-36) [54]. The SF-36 is a generic instrument for assessing health-related quality of life. It contains 36 items grouped into 8 dimensions: physical functioning, physical role, body pain, general health, vitality, social functioning, emotional role, and mental health. The scores range from 0 to 100 in every dimension, where higher scores indicate better health.

*The Beck Depression Inventory-II *[55,56] will be used to assess depression severity. It contains 21 items and the range of score is 0-63 with higher score indicating greater depression.

*The State Trait Anxiety Inventory-I *[57] will be used to assess the level of current anxiety. It is a 20-item self-administered questionnaire; the range of score is 20-80, with higher scores indicating a greater state of anxiety.

Positive health will be assessed by means of the following questionnaire:

*The Trait Meta-Mood Scale *[58], is comprised of three subscales and we will use only one of them, the mood repair scale (8 items), that assesses how well individuals regulate their moods and repair negative emotional experiences (e.g. "when I become upset, I remind myself of all the pleasures in life"). Participants rate their responses using a 5-point Likert type scale, with 1 = "strongly disagree" to 5 = "strongly agree".

*The Positive and Negative Affectivity Schedule *[59,60] is a 20-item questionnaire designed to measure positive and negative affectivity. The questionnaire includes 10 positive and 10 negative emotional states that should be answered on a 5-point Likert scale. The negative and positive subscales represent two relatively independent scales.

*The Satisfaction With Life Scale *[61,62] designed to assess global life satisfaction. The SWLS consists of five items with a 7-point Likert-scale from "strongly disagree" to "strongly agree". Higher scores reflect greater subjective well-being.

*The Life Orientation Test Revised *[63,64], is a 10-item scale that assesses subjects' expectations about their future and their general sense of optimism. It is comprised of 3 positively worded (e.g., "I'm always optimistic about my future"), 3 negatively worded items (e.g. "I hardly ever expect things to go my way") and the other 4 are filler questions. Each item is rated on a five-point Likert type scale ranging from one ("strongly disagree") to five ("strongly agree"). The higher the score obtained in the test, the higher the level of dispositional optimism is and vice-versa.

#### Cognitive function

*The Mini Mental State Examination *(MMSE) [65] will be used to evaluate cognitive capacity and severity of dementia for the exclusion criteria. The MMSE is a brief cognitive screening test. The MMSE asks questions that assess five areas of cognitive functioning: orientation, immediate memory, attention/concentration, delayed recall and language.

*The Paced Auditory Serial Addition Task *[66] will be used to measure sustained and divided attention, auditory information processing speed, and stimulus competition filtering skill. In this study, it will be administered only at the slowest presentation rate of 2.4 s. The score is the number of correct responses over 60 trials.

*The Rey Auditory Verbal Learning Test *[67] measures immediate free recall, delayed free recall, delayed recognition, and verbal learning. This is a multiple-trial verbal list learning test and will be given on an individual basis.

#### Patient global impression of change

We will also assess the patients' perception of change after the exercise interventions with *Patient Global Impression of Improvement scale *[68]. This is a scale used by patients to report their overall assessment of change during a clinical trial that uses a 7-point rating scale with the options "very much improved", "much improved", "minimally improved", "no change", "minimally worse", "much worse" and "very much worse".

### Assessment

The outcomes will be assessed just before the intervention (baseline), after 24 weeks of exercise interventions (post-intervention) and after 12 weeks of training cessation (detraining). The assessments of the primary and secondary outcomes will be performed on two separate days in order to prevent fatigue in the patients. The patients will complete some questionnaires at home between day 1 and 2. The study assessment schedule is shown in Table 2.

**Table 2 T2:** Study Assessment Schedule

Assessment	Screening	Baseline	Intervention	Post-intervention (24 weeks)	Detraining (12 weeks)
- Informed Consent	X				

*Day 1 testing*					
- Sociodemographic data	X			X	X
- Mini Mental State Examination	X				
- Physical Activity Readiness Questionnaire-PAR-Q	X				
- Beck Depression Inventory-II	X			X	X
- Tender points	X			X	X
- Visual analogic scale for pain		X	X	X	X

*Questionnaires to complete at home between day 1 and 2*					
- Fibromyalgia Impact Questionnaire		X		X	X
- Short-Form Health Survey 36		X		X	X
- State Trait Anxiety Inventory-I		X		X	X
- Trait Meta-Mood Scale		X		X	X
- Positive and Negative Affectivity Schedule		X		X	X
- Satisfaction With Life Scale		X		X	X
- Life Orientation Test Revised		X		X	X
- Pittsburgh Sleep Quality Index		X		X	X
- Multidimensional Fatigue Inventory		X		X	X
- ALPHA Environmental questionnaire		X		X	X
- Sedentary Behavior Questionnaire		X		X	X
- Physical activity at homework or workplace instrument		X		X	X
- Leisure time physical activity instrument		X		X	X
- International Fitness Scale		X		X	X
- Chronic Pain Self-Efficacy Scale		X		X	X
- Pain Catastrophizing Scale		X		X	X

*Day 2 testing*					
- Paced Auditory Serial Addition Task		X		X	X
- Rey Auditory Verbal Learning Test		X		X	X
- Body composition		X		X	X
- Chair sit and reach test		X		X	X
- Back scratch test		X		X	X
- Arm curl test		X		X	X
- 30-s chair stand test		X		X	X
- 8 ft up and go test		X		X	X
- Handgrip strength		X		X	X
- 6-min walk test		X		X	X
- Accelerometry (1 week)		X		X	X

- Patient Global Impression of Improvement scale				X	

### Familiarization and reliability assessment

Before the start of the study all patients will have a familiarization period with all the functional capacity tests, consisting of two ~50-min sessions. Each session will be preceded by a warm-up and will end with a cool-down of the same activities and duration used during the training period. Each familiarization session will consist of 2-3 sets of 1-3 repetitions of the exercises. We will also assess test-retest reliability (2-weeks apart) of the study functional capacity tests in a sub-sample. The tests will be performed by trained and qualified researchers.

### Assessment of side effects

We will record adverse effects or health problems attributable to the testing sessions or intervention sessions, including muscle pain, fatigue, and general aches and pains by self-report during the study period. An independent researcher will be in charge of auditing all assessment staff to record all these events in the participants over the study period.

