### Randomisation and blinding

The participant randomisation assignment will follow an allocation concealment process, that is, the researcher in charge of randomly assigning participants will not know in advance which treatment the next person would receive and will not participate in assessment. Assessment staff will be blinded to participant randomisation assignment. Participants will be explicitly informed on the group to which they will be assigned as well as on the study hypotheses and will be reminded not to discuss their randomisation assignments with assessment staff. It will not be possible to conceal the group assignment from the staff involved in the training.

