## Implications of the hypothesis

The *al-Andalus *physical activity RCT will investigate the effects of 24-week land- and water-based exercise interventions on disease impact, tenderness, body composition, functional capacity, quality of life and cognitive function in female patients with fibromyalgia. Both exercise interventions will include aerobic, strengthening and flexibility exercises. We will also assess the effect of a 3-month detraining period on the study primary and secondary outcomes. To our knowledge, this is the largest study specifically designed to compare the effect of a water-based and land-based exercise interventions on fibromyalgia patients. Our study attempts to reduce impact of fibromyalgia and improve patients' health status and quality of life by implementing two types of exercise interventions. Results from this study will help to better assess the potential of exercise interventions in the treatment of fibromyalgia. If the interventions proved to be effective and safe, this study would provide low-cost and feasible alternatives for health professionals in the management of fibromyalgia.

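### Adverse effects are recorded only if attributable to a session, so discrete events cannot be compared like for like between arms, and the unclear recording route puts assessor blinding at risk

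*Protocol article*

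**What the plan says.** Assessment of side effects sets the rule for what is captured: "We will record adverse effects or health problems attributable to the testing sessions or intervention sessions". It names the kinds of event and their source: "including muscle pain, fatigue, and general aches and pains by self-report during the study period". On the recording route it says: "An independent researcher will be in charge of auditing all assessment staff to record all these events in the participants over the study period".

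Randomisation and blinding says of the same staff: "Assessment staff will be blinded to participant randomisation assignment". Participants know their group and the study hypotheses, and they "will be reminded not to discuss their randomisation assignments with assessment staff". Of the trainers it says: "It will not be possible to conceal the group assignment from the staff involved in the training".

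Under Interventions, both exercise groups train three times a week for 24 weeks. Under Usual care group, controls receive general advice and pamphlets and have no sessions. Implications of the hypothesis looks ahead to use in practice with the condition "If the interventions proved to be effective and safe".

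**The concern.** Two things are at stake.

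The first is the comparison of harms. The rule filters events by cause before they are written down, and most of the causes that qualify exist only in the exercise arms. In this disease the filter is also a poor one, because the named events are part of the condition. A woman who has a bad week after a session, and whoever records it, cannot tell exercise from fibromyalgia in her single case. Comparing all events by randomised arm can separate the two; a list of attributed events cannot.

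The second is blinding. If assessment staff take down the events, a woman who reports soreness after a pool or gym session has told them that she is not a control. Testing the hypothesis has the same investigators perform baseline and follow-up examinations, so an assessor who learned the allocation at 24 weeks would still know it at the detraining visit.

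**Working it through.** The plan gives no event rate or safety sample size, so there is no figure to reproduce. The check counts the occasions on which an event can qualify, then sets the sections side by side.

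**1. Qualifying occasions after randomisation, per participant**

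Inputs: 3 sessions a week for 24 weeks (Interventions); two test days per assessment, with follow-up assessments at 24 weeks and after 12 weeks of detraining (Assessment, Table 2); allocation after baseline measurements (Testing the hypothesis); familiarisation before the study starts (Familiarization and reliability assessment).

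| | Exercise arms | Control |
|---|---|---|
| Scheduled exercise sessions | 3 × 24 = 72 | 0 |
| Follow-up test days | 2 × 2 = 4 | 2 × 2 = 4 |
| Total | 76 | 4 |

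The four test days fall at or after the end of training. During the 24 weeks themselves the count is therefore 72 against 0. These are opportunities, not events. Make-up sessions may shift when sessions are held, and the retest sub-sample may add a few test occasions, since its timing is not given.

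**2. What the attribution filter does**

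Let *p* be the proportion of women with a flare outside test days, the same in every arm (exercise has no effect). Let *a* be the share of those flares that is attributed to a session in an exercise arm. The documents give neither value.

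- Recorded in an exercise arm: *p* × *a*
- Recorded in the control arm: 0, because no session exists to attribute the flare to
- Recorded difference: *p* × *a*, anywhere from 0 to *p*, when the true difference is 0

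Now let exercise add a true excess *d*. The record shows *a* × (*p* + *d*) against 0, and this falls to 0 if every flare is put down to the disease (*a* = 0). The recorded contrast thus depends on an unknown attribution habit, and the error can go either way.

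**3. Overlap with the disease**

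Background lists pain, fatigue, stiffness, low back pain and muscle spasm among the features of fibromyalgia. The section on side effects names muscle pain, fatigue and aches. These overlap almost entirely, so *a* cannot be judged well for an individual woman.

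**4. What other data are collected in controls**

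The only item that Table 2 schedules during the intervention is the pain scale, and the text ties its use in that period to before and after each session. Controls have no sessions, so no scheduled contact with them captures events in those 24 weeks. At 24 weeks and after detraining, all arms complete the outcome scales.

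**5. Who records**

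The sentence on the independent researcher has two readings: assessment staff record and the researcher audits them, or the researcher makes the record. Under the first, reports of exercise-session events reach blinded staff, against the intent of Randomisation and blinding. Under the second, the outcome depends on whether the researcher obtains the information through those staff or directly from participants, which the text does not say.

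**The case against.** A reader might infer that harms have no control comparison at all. The documents do not support that. Events attributable to testing can arise in every arm. More importantly, pain and fatigue are measured in all arms without any attribution filter: the FIQ items, the pain scale, tender points and algometer score, the fatigue inventory and SF-36 body pain. The Statistical analysis section compares these by group under intention to treat. A lasting average worsening of pain or fatigue from exercise would show there. What these scales do not count is discrete events: flares that have settled by the visit, injuries, and other health problems between visits.

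A reader might also infer that blinding is broken. The text does not show this. The sentence is ambiguous, self-report need not go to the assessors, and participants are reminded not to disclose their group. Nor is the primary outcome exposed by this route, because the FIQ is self-administered and completed at home.

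Finally, the article does not commit itself to a safety conclusion. The phrase about being safe is a conditional remark in the closing section, and safety is in neither the Objectives nor the hypotheses.

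It is also fair to say that forms and calling intervals are details that a journal article leaves to the full protocol. The restriction to attributable events is different: it is a stated rule, not an omission. That part stands.

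**Conclusion.** The point holds in limited form. Followed as written, the rule yields discrete-event data that cannot be compared like for like: 72 scheduled exercise sessions per participant against none, with attribution resting on symptoms that the disease itself produces. The size of any distortion cannot be stated, because it depends on a flare rate and an attribution share that the documents do not give. It could create an apparent excess or hide a real one.

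The conflict with blinding is a risk that depends on how one sentence is read. If assessors do record the events, the outcomes exposed are those that staff measure after baseline, such as tender points and fitness tests.

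The primary efficacy comparison is not affected by either part. The change is worth making because any later statement about safety would lean on these records, and the remedy is cheap.

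**What to change.** Revise Assessment of side effects as follows:

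- Record all adverse events and health problems in all three arms, irrespective of presumed cause.
- Ask the same questions at the same times in every arm. Trainers see exercise participants three times a week, so notes made only at sessions would bring the imbalance back.
- Keep attribution to a testing or exercise session as a secondary field.
- Report events by randomised arm.
- Have existing staff other than the blinded outcome assessors collect events. The trainers already know the allocation, and the exercise monitor already has contact with controls.
- Reword the sentence on the independent researcher so that it says who records and who audits, and reconcile it with Randomisation and blinding.

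The cost is a short event form, a matching periodic enquiry to controls, and more events to log, many of them ordinary disease symptoms. Outcome measures, sample size and efficacy analysis do not change.

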## Implications of the hypothesis

The *al-Andalus *physical activity RCT will investigate the effects of 24-week land- and water-based exercise interventions on disease impact, tenderness, body composition, functional capacity, quality of life and cognitive function in female patients with fibromyalgia. Both exercise interventions will include aerobic, strengthening and flexibility exercises. We will also assess the effect of a 3-month detraining period on the study primary and secondary outcomes. To our knowledge, this is the largest study specifically designed to compare the effect of a water-based and land-based exercise interventions on fibromyalgia patients. Our study attempts to reduce impact of fibromyalgia and improve patients' health status and quality of life by implementing two types of exercise interventions. Results from this study will help to better assess the potential of exercise interventions in the treatment of fibromyalgia. If the interventions proved to be effective and safe, this study would provide low-cost and feasible alternatives for health professionals in the management of fibromyalgia.

## Abbreviations

ANCOVA: Analysis of covariance; FIQ: Fibromyalgia impact questionnaire; MMSE: Mini Mental State Examination; PAR-Q: Physical Activity Readiness Questionnaire; RCT: Randomised controlled trial; RPE: Rate of perceived exertion; SF-36: Short-form 36 items.
